## Abstract

**Aim:**

There is a current lack of evidence in the literature to support the routine use of negative pressure wound therapy (NPWT) to reduce the risk of surgical site infections (SSI) in the setting of ileostomy or colostomy reversal. The aim of this study is to examine whether routine NPWT confers a lower rate of SSI than conventional dressings following reversal of ileostomy or colostomy.

**Methods:**

The PRIC study is a randomized, controlled, open-label, multi-centre superiority trial to assess whether routine NPWT following wound closure confers a lower rate of SSI following reversal of ileostomy or colostomy when compared to conventional dressings. Participants will be consecutively identified and recruited. Eligible participants will be randomized in a 1:1 allocation ratio, to receive either the NPWT (PREVENA) dressings or conventional dressings which will be applied immediately upon completion of surgery. PREVENA dressings will remain applied for a duration of 7 days. Surgical wounds will then be examined on post-operative day seven as well as during follow-up appointments in OPD for any evidence of SSI. In the interim, public health nurses (PHN) will provide out-patient support services incorporating wound assessment and care as part of a routine basis. Study investigators will liaise with PHN to gather the relevant data in relation to the time to wound healing. Our primary endpoint is the incidence of SSI within 30 days of stoma reversal. Secondary endpoints include measuring time to wound healing, evaluating wound healing and aesthetics and assessing patient satisfaction.

**Conclusion:**

The PRIC study will assess whether routine NPWT following wound closure is superior to conventional dressings in the reduction of SSI following reversal of ileostomy or colostomy and ascertain whether routine NPWT should be considered the new standard of care.

## Introduction

Surgical site infections (SSI) remain one of the most common complications following reversal of ileostomy and colostomy [1, 2]. They contribute to a longer length of stay and increased healthcare expenditure and pose adverse psychological effects on patients [3, 4]. The use of various skin closure techniques has been studied with the aim of reducing SSI, for example, the purse-string closure method has been reported to have considerable success [5, 6]. Similarly, the use of routine negative pressure wound therapy (NPWT) has been postulated as an alternative method to mitigate the risk of developing SSI [7–11].

PREVENA Therapy is a form of incisional negative pressure wound therapy (I-NPWT) that has been widely used in the management of closed surgical incisions. PREVENA Incision Management System is a type of disposable, customizable and powered negative pressure system designed to help manage and protect surgical incisions and their surrounding environment. These dressings are designed to hold incision edges together, as well as remove both fluids and infectious agents. They act as a barrier to external contamination by delivering a continuous negative pressure of 125 mmHg for up to 7 days [12]. Physiologically, they promote wound healing by increasing tissue granulation, promoting angiogenesis and increasing perfusion to tissue via fluid evacuation [13].

In recent years, there have been multiple studies comparing the use of PREVENA Therapy to conventional dressings in the management of surgical wounds, particularly in the setting of vascular surgeries, post-caesarean infections and colorectal resections [14–19]. To date, there is a lack of evidence to support the routine use of NPWT or PREVENA Therapy in the setting of stoma reversal. Patients undergoing elective reversal of ileostomy or colostomy are deemed vulnerable to developing SSI. In view of the significant patient morbidity and healthcare burden associated with SSI as well as the potential impact of PREVENA Therapy in reducing these complications, this study aims to assess whether routine NPWT is superior to conventional dressings in the prevention of SSI.

## Methods

PRIC study is registered on the ClinicalTrials.gov platform—NCT0497493. Approval by the Research Ethics Committee at St. James’s Hospital/Tallaght University Hospital has been granted.

### Study setting and design

This study is designed as a randomized, controlled, open-label, multi-centre superiority trial with two parallel groups with a primary endpoint of measuring SSI incidence within 30 days of reversal of ileostomy or colostomy. The trial will be conducted at two centres located in Dublin, Ireland: St James’s Hospital and Tallaght University Hospital.

### Objectives

The primary aim of PRIC study is to examine whether routine NPWT (PREVENA) confers a lower rate of surgical site infections than conventional dressings following reversal of loop ileostomy or colostomy. The secondary objectives of PRIC study are:To assess if NPWT confers a shorter time to wound healingTo assess patient experience and satisfaction with NPWT and conventional dressingsTo assess wound aesthetics

### Inclusion criteria

PRIC Study will include patients who are electively admitted to St. James’s Hospital or Tallaght University Hospital for reversal of loop ileostomy or colostomy. Patients must be 16 years of age or older and consent to the follow-up protocols.

### Exclusion criteria

Patients will be excluded from the PRIC Study if they are less than 16 years of age at screening or if they fail to attend for their regular OPD follow-up appointments. Patients will also be excluded and recorded as treatment failures if dressings, either PREVENA or conventional, are removed outside of their defined time periods.

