### Interventions

Following selection and attainment of informed consent, all participants will be randomly assigned to either the PREVENA therapy group or conventional dressings group with a 1:1 allocation ratio via stratified randomisation. Participants will be stratified by their baseline comorbidity state and will be stratified into one of the three groups, namely:i)No diabetes nor immunosuppressant useii)Diabetic patients (both insulin, non-insulin dependent, type one or type two)iii)Use of immunosuppressants

Following stratification, participants will be systematically randomized in a 1:1 allocation ratio into either the PREVENA group or the conventional dressing group. The conventional dressings that are used in the study will be non-antimicrobial, standard surgical dressing. On the day of elective admission, the relevant primary or co-investigators will perform this randomisation by picking one of the sealed envelopes containing the assignment. There will be equal proportion of assignments to either group (PREVENA and conventional dressings) to achieve a 1:1 allocation ratio. The conventional dressings that are used in the study will be non-antimicrobial, standard adherent surgical dressing. Due to the nature of the intervention, neither the participants nor the staff can be blinded to allocation. Prophylactic antibiotics will be administered following reversal surgeries as per local guidelines. Initial dose will be administered during induction of the surgeries, followed by three more doses administered post-operatively. Wound closure will be performed in a standardized manner, and the randomized dressing will be applied immediately after wound closure. The PREVENA dressings will be left in situ for 7 days at which point the wound will be inspected for any evidence of SSI. Wound swabs will be performed for culture and sensitivity for any incidence or suspicion of SSI.

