Criteria for discontinuing PREVENA Therapy include post-operative complications requiring removal of PREVENA dressings or requiring surgical re-intervention. A number of possible risks associated with the use of negative pressure dressing PREVENA will be monitored which include but are not limited to discomfort with application or re-application, skin irritation or reaction to dressing materials used, wound bleeding, infection and retained dressing material. Surgical site wounds will be closely monitored, and should any of these occurrences arise, they will be promptly managed and treated. We acknowledge and permit certain relevant concomitant care such as the use of nutritional supplements. Nutritional supplements will be permitted to participants if deemed beneficial or necessary by a dietitian.

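### Patients are excluded after randomisation for dressing removal or a missed clinic visit, which leaves the primary SSI comparison open to bias

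*Protocol article*

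**What the plan says.** The Exclusion criteria section contains two rules that act on events during follow-up. Patients are excluded "if they fail to attend for their regular OPD follow-up appointments", and for dressing removal: "Patients will also be excluded and recorded as treatment failures if dressings, either PREVENA or conventional, are removed outside of their defined time periods".

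The Interventions section fixes the timing: "On the day of elective admission, the relevant primary or co-investigators will perform this randomisation". The dressing goes on after wound closure. On wear time it says "The PREVENA dressings will be left in situ for 7 days". On stopping the device it says: "Criteria for discontinuing PREVENA Therapy include post-operative complications requiring removal of PREVENA dressings or requiring surgical re-intervention". A separate list of risks to be monitored includes "wound bleeding, infection and retained dressing material". The same section states that neither participants nor staff can be blinded.

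Under Outcomes, the primary endpoint is investigator-assessed SSI within 30 days of reversal, confirmed by culture. Data collection and management places the outpatient visit about 30 days after discharge. It has the home nurses refer any concern back to the investigators, who reassess the wound and confirm by culture. Data analysis names a chi-squared test between the two randomised groups. No section says that excluded patients stay in that test.

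**The concern.** An exclusion criterion normally describes something known before allocation. These two describe what happens afterwards, so applying them removes randomised patients from a superiority comparison. That is harmless only if removal from the analysis works in the same way in both arms, and the article gives reasons for doubt:

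- Complications are a stated reason for taking PREVENA off, and the primary outcome is itself a post-operative complication.
- Removal is decided with the arm known.
- The clinic visit comes after the endpoint window has closed. Thirty days from discharge is at or beyond 30 days from surgery, so a patient whose SSI was confirmed earlier through nurse referral can still be excluded for missing that visit.

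At stake is whether an observed difference in SSI can be attributed to the dressing, in a trial meant to inform whether NPWT becomes standard care.

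**Working it through.** **Inputs from the article.** SSI 25% v 10%, two-sided α 0.05, power 0.80, 1:1 allocation, 10% dropout (Sample size; Data analysis; Interventions).

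**Input not in the article.** The proportions excluded. Those below are assumptions.

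**1. The plan's own figure.** With pooled variance and no continuity correction,

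n = [1.96·√(2·0.175·0.825) + 0.8416·√(0.25·0.75 + 0.10·0.90)]² / 0.15² = 99.5, that is 100 per arm, as stated.

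200/0.9 = 222.2, against the stated 222 or so, hence 111 per arm. The sample size is not at fault.

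**2. Effect of exclusion on the observed rate.** Let p be the true SSI rate, f the share of infected patients excluded and g the share of uninfected patients excluded.

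- Retained fraction: k = p(1−f) + (1−p)(1−g)
- Observed rate: q = p(1−f)/k

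**3. Rejection probability.** For the uncorrected chi-squared test, with n = 111k in each arm and d the difference in q,

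P = Φ[(d − 1.96·SE₀)/SE₁] + Φ[(−d − 1.96·SE₀)/SE₁],

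where SE₀ is the pooled and SE₁ the unpooled standard error.

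**4. No true effect (p = 0.25 in both arms).**

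| Excluded: infected NPWT / infected control / uninfected (both arms) | Observed NPWT v control | Type I error |
|---|---|---|
| 5% / 5% / 5% | 25.0% v 25.0% | 5.0% |
| 20% / 10% / 5% | 21.9% v 24.0% | about 6.5% |
| 20% / 5% / 5% | 21.9% v 25.0% | about 8% |
| 30% / 5% / 5% | 19.7% v 25.0% | about 15% |

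Second row in full:

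- NPWT: 0.25·0.80 = 0.200 and 0.75·0.95 = 0.7125, so q = 0.200/0.9125 = 0.2192 and n = 101.3.
- Control: 0.25·0.90 = 0.225, so q = 0.225/0.9375 = 0.2400 and n = 104.1.
- d = 0.0208 and both SEs are 0.0587. P = 0.064 by the formula, or 0.065 by exact enumeration of the test.

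Last row: NPWT q = 0.175/0.8875 = 0.1972 with n = 98.5; control 0.25 with n = 105.4; d = 0.0528, SE₀ = 0.0585, SE₁ = 0.0582, P = 0.146.

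**5. What drives the error.** It is a difference between arms in who is lost. If the same share of infected patients is lost in both arms (20%, 30% or 50%, nobody else excluded), the exact type I error stays at 4.9% to 5.0%.

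**6. Direction is not fixed.** If instead 20% of uninfected NPWT patients lose the dressing early (for discomfort or leakage, say) and 5% of everyone else is excluded, the NPWT rate becomes 0.2375/(0.2375 + 0.75·0.80) = 0.2375/0.8375 = 28.4% against 25%. That works against NPWT.

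**The case against.** The best defence is that the article gives no removal or non-attendance rates, so it cannot show that bias occurs. That stands: the plan is open to bias, and the documents do not show that its result will be biased. It is also fair that analysis sets are often left to a SAP, which is not shown, and that the test is described as comparing the randomised groups. But an exclusion rule stated outright in the protocol would conflict with any later analysis of all randomised patients, and outcomes not collected after exclusion may not be recoverable.

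A reader might infer more than the documents support in these respects:

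- **That infected NPWT patients are removed because of the infection.** Infection is in the list of monitored risks, and the text does not say that it leads to removal. The link runs through complications requiring removal. An SSI that arises after day 7 cannot cause early removal of PREVENA.
- **That type I error reaches 10%, 17% or 45%.** These figures are arithmetically right at 100 per arm when 20%, 30% or 50% of infected NPWT patients are excluded. They assume that nobody else in the trial is excluded, although the rule covers both dressings, so they are close to a worst case.
- **That missed visits are linked to infection or to arm.** This is plausible but stated nowhere.
- **That the rule cannot act equally because only PREVENA has a stated wear time.** The rule presupposes defined periods for both dressings. A condensed article may simply omit the second.
- **That removals would count as primary events.** The endpoint is culture-confirmed SSI and does not include treatment failure. The natural reading is that such patients leave the comparison and the failure is logged, which is not a contradiction.
- **That nurse visits already supply SSI status.** Nurses refer concerns; investigators assess and confirm.

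**Conclusion.** The point holds as a flaw in the rule as written. Two exclusion criteria act after randomisation. One is tied, in the PREVENA arm, to post-operative complications under open-label conditions. The other can discard a patient whose SSI is already known. No section restores the randomised set.

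Under no true effect, with 25% SSI and 111 per arm, type I error ranges from about 5% (exclusion alike in both arms) through 6.5% and 8% to about 15% for the patterns examined. All of these rest on assumed exclusion rates, and a different pattern can push the estimate against NPWT. The 10% dropout inflation protects the number of patients but not the comparability of the arms.

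**What to change.** 1. Limit the exclusion criteria to features known before randomisation, and delete the two that depend on dressing removal and clinic attendance.
2. Define the primary analysis as all randomised patients in their allocated arm, using investigator-assessed SSI status to day 30 whatever happened to the dressing or the clinic visit. Randomisation precedes surgery, so if patients who never have the reversal are left out, call the set modified intention-to-treat.
3. Keep following patients after early removal. For those who miss the clinic visit, use the existing nurse-referral route to investigator assessment and the hospital records. Treat any status still unknown as missing data, with a sensitivity analysis.
4. Report early removal as a separate adherence or device outcome, and state that treatment failure is not part of the SSI endpoint.
5. Give the worn-as-planned set only as a sensitivity analysis.

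The cost is protocol wording, somewhat more follow-up and analysis work, and possibly a smaller estimated effect. No extra patients are needed: 100 per arm is unchanged, and if all 111 per arm are analysed, power at 25% v 10% is about 0.84.

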### Patient identification and consent

Patients undergoing reversal surgeries will be assessed in outpatient clinics in SJH and TUH prior to admission for these elective procedures. Eligible participants will be identified and recruited. Explanation regarding PRIC study as well as a patient information leaflet will be provided during these visits, and eligible participants will have a period of time prior to elective admission to consider their participation. All patient participants must provide written informed consent to enter this study. The PRIC Study enrolment will commence on the 1st of May 2022 at both SJH and TUH.

### Interventions

Following selection and attainment of informed consent, all participants will be randomly assigned to either the PREVENA therapy group or conventional dressings group with a 1:1 allocation ratio via stratified randomisation. Participants will be stratified by their baseline comorbidity state and will be stratified into one of the three groups, namely:i)No diabetes nor immunosuppressant useii)Diabetic patients (both insulin, non-insulin dependent, type one or type two)iii)Use of immunosuppressants

Following stratification, participants will be systematically randomized in a 1:1 allocation ratio into either the PREVENA group or the conventional dressing group. The conventional dressings that are used in the study will be non-antimicrobial, standard surgical dressing. On the day of elective admission, the relevant primary or co-investigators will perform this randomisation by picking one of the sealed envelopes containing the assignment. There will be equal proportion of assignments to either group (PREVENA and conventional dressings) to achieve a 1:1 allocation ratio. The conventional dressings that are used in the study will be non-antimicrobial, standard adherent surgical dressing. Due to the nature of the intervention, neither the participants nor the staff can be blinded to allocation. Prophylactic antibiotics will be administered following reversal surgeries as per local guidelines. Initial dose will be administered during induction of the surgeries, followed by three more doses administered post-operatively. Wound closure will be performed in a standardized manner, and the randomized dressing will be applied immediately after wound closure. The PREVENA dressings will be left in situ for 7 days at which point the wound will be inspected for any evidence of SSI. Wound swabs will be performed for culture and sensitivity for any incidence or suspicion of SSI.

Criteria for discontinuing PREVENA Therapy include post-operative complications requiring removal of PREVENA dressings or requiring surgical re-intervention. A number of possible risks associated with the use of negative pressure dressing PREVENA will be monitored which include but are not limited to discomfort with application or re-application, skin irritation or reaction to dressing materials used, wound bleeding, infection and retained dressing material. Surgical site wounds will be closely monitored, and should any of these occurrences arise, they will be promptly managed and treated. We acknowledge and permit certain relevant concomitant care such as the use of nutritional supplements. Nutritional supplements will be permitted to participants if deemed beneficial or necessary by a dietitian.

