### Data analysis

Data analysis, processing and calculation of inferential statistics will be performed primarily using SPSS software. In relation to primary endpoint analysis, which assesses the presence of SSI within 30 days following reversal surgeries, a Chi-squared test will be used to compare the SSI incidence rates between the two randomized groups (PREVENA vs conventional surgical dressings). The time to wound healing, patient experience and satisfaction and the degree of wound healing and wound aesthetics will be presented as secondary outcomes. A t-Test will be applied to compare the time to wound healing between the randomized groups as appropriate. Similarly, t-Test will be applied to compare the level of satisfaction between patients of the randomized groups. All outcome measures will be presented with 95% confidence intervals and two-sided test *p* values.

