### Subgroup analysis

We intend to conduct a subgroup analysis given the strong biological rationale and potential interaction effects these variables may have on measured outcomes. These variables include age, presence of co-morbidities such as diabetes mellitus and the use of immunosuppressants which may impair the process of wound healing.

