## Discussion

At present, there is a lack of consensus on the routine use of NPWT in the setting of stoma reversal. To date, there have been four randomized trials that have investigated the use of NPWT in stoma reversal, and the results from these studies are conflicting and inconclusive. The NEPTUNE trial observed that the prophylactic use of NPWT was not associated with a decrease in 30-day SSI incidence rate when compared to standard dressings, with the 30-day SSI incidence of the NPWT group being 32% versus 34% in the standard dressing group [17]. Uchino et al. also noted no difference in the efficacy rates between the use of NPWT and purse-string suture methods in preventing SSI [21]. Similarly, Carrano et al. reported similar incidence rates of SSI and wound complications in both the NPWT and conventional dressing cohorts [22]. In contrast, the trial conducted by Wierdak et al. reported a positive benefit in the use of prophylactic NPWT in the setting of ileostomy closure, with a reduced incidence of SSI and wound healing complications. They had a SSI incidence of 5.7% in the NPWT group versus 22.2% in the standard dressing cohort [23]. Similarly, wound healing complications, defined as any condition of the wound that required post-operative intervention other than a change of dressing or removal of stiches, were significantly lower in the NPWT group (8.6% versus 30.6%) [23]. In addition to these conflicting results, these studies are not sufficiently powered, thereby supporting the need for further evaluation and support the relevance of PRIC Study in establishing whether the routine use of NPWT does reduce SSI rate when compared to using conventional dressings.

In addition, current literature lacks research studies that employ microbiology wound swabs and culture in their assessment of SSI. PRIC Study will involve the use of microbiology wound swab, culture and sensitivity to help improve the accuracy of assessing and reporting SSI incidence. And to our knowledge, the PRIC Study is the first study that employs microbiological wound swabs in assessing SSI in the setting of reversal of ileostomy and colostomy surgeries.

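### Stoma type and hospital enter neither the stratification, the primary test nor the named subgroups: a modest loss of precision and interpretability, not bias

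*Protocol article*

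**What the plan says.** Under Inclusion criteria the Protocol article admits patients "electively admitted to St. James’s Hospital or Tallaght University Hospital for reversal of loop ileostomy or colostomy". Study setting and design adds: "The trial will be conducted at two centres located in Dublin, Ireland".

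Interventions sets out the allocation. "Participants will be stratified by their baseline comorbidity state and will be stratified into one of the three groups": neither diabetes nor immunosuppressants, diabetes, or immunosuppressant use. After that, "participants will be systematically randomized in a 1:1 allocation ratio", and investigators "perform this randomisation by picking one of the sealed envelopes containing the assignment". The section does not mention hospital or stoma type as a factor.

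For the primary endpoint, Data analysis states that "a Chi-squared test will be used to compare the SSI incidence rates between the two randomized groups", with no covariate or stratum. Under Subgroup analysis, "These variables include age, presence of co-morbidities such as diabetes mellitus and the use of immunosuppressants". Neither stoma type nor hospital is named there.

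**The concern.** Stoma type divides the eligible population into two different operations, and hospital divides it into two sets of surgeons and endpoint assessors. Both are known before randomisation. If either is related to SSI risk, the arms can differ on it by chance. The stated scheme does not limit that difference, and the stated test does not remove it from the estimate.

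The second issue is interpretation. The abstract's conclusion asks whether routine NPWT should become standard after reversal of either kind of stoma. The one positive stoma-reversal trial in the Discussion "reported a positive benefit in the use of prophylactic NPWT in the setting of ileostomy closure", with SSI of 5.7% against 22.2%. Without a planned estimate by stoma type, a reader of the PRIC result could not see whether the effect was similar in the two operations.

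**Working it through.** **The plan's own figure.** Inputs from Sample size and Data analysis: SSI 25% against 10%, power 0.80, two-sided α 0.05. With pooled variance under the null and no continuity correction:

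n per arm = [1.96·√(2·0.175·0.825) + 0.8416·√(0.25·0.75 + 0.10·0.90)]² / 0.15² = 99.5, so 100.

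The stated 100 per arm is reproduced, and power at that size is 80.2%. Allowing for dropout, 200/0.9 = 222.2, as stated.

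**Chance imbalance.** The article gives no share of colostomies, no split by hospital and no SSI rate by either, so the share q and the risk gap g are assumptions. For a factor not used in allocation, the between-arm difference in its share has SD = √(2q(1−q)/100). The probabilities use the normal approximation. The shift in the SSI difference is imbalance × g.

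| Minority share q | SD (points) | 95% range (points) | Chance of ≥10 points | Shift at the 95% limit for g = 5 / 10 / 15 points | Power for 25% v 10% in the smaller group |
|---|---|---|---|---|---|
| 10% | 4.2 | ±8.3 | 2% | 0.42 / 0.83 / 1.25 | 14% |
| 20% | 5.7 | ±11.1 | 8% | 0.55 / 1.11 / 1.66 | 23% |
| 30% | 6.5 | ±12.7 | 12% | 0.64 / 1.27 / 1.91 | 33% |
| 50% | 7.1 | ±13.9 | 16% | 0.69 / 1.39 / 2.08 | 51% |

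An imbalance of exactly 10 points with g of 15 to 20 points gives 0.10 × 15 = 1.5 to 0.10 × 20 = 2.0 points, or 10% to 13% of the planned 15. Pairing both extremes (13.9 points and g = 20) would give 0.139 × 20 = 2.8 points.

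**Scale against the sampling error.** The standard error of the planned difference is √(0.25·0.75/100 + 0.10·0.90/100) = 5.3 points, so a shift of 1.5 to 2.0 points is 0.3 to 0.4 standard errors. With g = 15 points in both arms, imbalance contributes (0.0566 × 15 / 5.27)² = 2.6% of the variance at q = 20% and (0.0707 × 15 / 5.27)² = 4.0% at q = 50%. That is about what adjustment for one such factor could recover.

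**Error rates.** In 100,000 simulated trials per scenario, the unadjusted test was applied with the factor left to chance or exactly balanced. Control risks in the two levels were 22% and 37% (q = 20%), 20% and 36.67% (q = 30%), and 20% and 30% (q = 50%). For power, treatment multiplied each risk by 0.4.

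- Type I error: 0.051, 0.050 and 0.049 left to chance; 0.047, 0.045 and 0.048 balanced.
- Power: 0.815, 0.815 and 0.817 left to chance; 0.816, 0.820 and 0.817 balanced.

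Balancing without adjusting hardly changes power and makes the test slightly conservative. Any gain needs the factor in the analysis as well.

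**The case against.** The strongest reply is that chance imbalance is not bias. Randomisation makes the comparison unbiased in expectation, and the planned confidence interval already includes this source of variation. The simulations agree. A reader might infer that pooling two operations at two hospitals invalidates the primary result; the documents and the arithmetic do not support that.

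Three other inferences also go too far.

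- *The effect has no cited support in colostomy reversal.* Sample size attributes 25% to 10% to published literature without naming a source. The Discussion describes four trials in stoma reversal and ties only one to ileostomy closure. The case mix of the others is not given, so this cannot be established.
- *The hospitals treat or assess patients differently.* Antibiotics follow local guidelines, but Interventions also describes one dosing pattern for all and a standardised wound closure. SSI is judged by CDC criteria with culture confirmation. Site differences are possible but not shown.
- *Both hospitals draw from one shared pool of envelopes.* The article does not say so. A fuller document may describe separate sets.

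The subgroup list is introduced as including certain variables, so it may be open, and a supporting adjusted analysis may be in an analysis plan not shown here. These points lower the weight of the concern but do not remove it. The article states its stratification factor and its primary test outright, and an analysis plan written later cannot add a stratification factor for patients already allocated.

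**Conclusion.** The point holds as a modest weakness in precision and interpretability. Two baseline characteristics that define who is enrolled and where are not used in the stated allocation, the stated primary test or the named subgroups. At assumed shares of 20% to 50%, an imbalance of 10 points or more arises in about 8% to 16% of trials (2% at a 10% share). The resulting shift is about 2 points at most under a 15-point risk gap at the 95% limit, or a 20-point gap with a 10-point imbalance, against a planned 15.

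These sizes depend on risk gaps that nothing in the article confirms; a gap of 15 to 20 points is as large as the planned treatment effect or larger. With a 5-point gap the shift stays below 1 point. The change is worth making because it costs little and because the intended conclusion covers both operations.

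**What to change.** 1. **Interventions.** Hold separate envelope sets for each hospital within the three comorbidity groups: 2 × 3 = 6 sets, averaging 222/6 = 37 patients. Use randomly varied block sizes that are not disclosed to investigators, because small fixed blocks in an open-label trial make the next assignment guessable. Do not also stratify by stoma type: 12 cells would average only about 17 patients at 200. Record stoma type before randomisation instead.
2. **Data analysis.** Make the primary comparison adjusted for hospital, comorbidity group and stoma type, for example by logistic regression with a standardised risk difference, or by Mantel-Haenszel. Keep the chi-squared test as supportive. The planning rates imply about 25 + 10 = 35 infections, and the regression would have five terms (arm, hospital, two for comorbidity, stoma type), so add no further covariates.
3. **Subgroup analysis.** Add stoma type, with an interaction test and the treatment effect with 95% CI for each type. Label it descriptive, since power in the smaller group is only about 14% to 51%.

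The cost is envelope preparation and a few lines of text; stoma type is already known, so no new data are needed. The downsides are some incomplete blocks and one more imprecise subgroup. Enrolment was due to open on 1 May 2022. If recruitment has started, make only changes 2 and 3, and fix them before anyone deciding on them has seen SSI by arm, which the month 6 interim analysis would show.
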